**Version No: 1.7**

**Affiliation of Principal Investigator: Department of Surgery, Seoul National University Hospital**

**Name of Principal Investigator: [name]**

**Summary**

| Title | (Korean) 항문 질환 수술 환자에서 기존 좌욕과 좌욕수류비데 시스템을 이용한 통증 관리 및 창상치유 효과와 편의성 비교를 위한 무작위배정, 다기관 비교 임상시험 |
| --- | --- |
|  | (English) Randomized Controlled, Multicenter Study to Evaluate the Efficacy and Convenience of Electronic Bidet with Low Force Flow Fountain System for Pain Control and Wound Healing after Operation for Anal Disease, Compared to Conventional Sitz Bath |
| Principal Investigator | Department of Surgery, Seoul National University College of Medicine, [name] [name] |
| Research Funding Organization | COWAY CO., LTD., Seoul National University College of Medicine Research Foundation |

| Study Objective | After operation for anal disease, sitz bathing is recommended for pain control and wound healing. However, the process of filling with water and draining of the conventional sitz bath is very cumbersome and difficult, so it is not easy to do it for patients with discomfort to move due to severe pain after surgery.  Like a sitz bath, bidet brings water into contact with the perianal area. Because of similarities between the sitz bath and the bidet, questions have been constantly raised whether a bidet could be used instead of a sitz bath. But, these effects of the bidet have not been studied up to date. Accordingly, we reported that bidets can have the same effect as sitz baths in reducing anorectal pressure in previous studies.  However, clinical studies comparing the effects of sitz baths and bidets are necessary to be applied to the treatment of patients in clinical practice. In this study, we tried to compare and analyze the efficacy and convenience for pain control and wound healing after operation for anal diseases using a bidet with a very low force water stream compared to the conventional sitz bath. |
| --- | --- |
| Study Design | Randomized Controlled, Multicenter Clinical Trial  (non-inferiority trial) |
| Study Duration | 2015.01.12 ~ 2019.01.11 |
| Subject of Study (test drug, etc.) | Patients who underwent a hemorrhoidectomy |
| Number of Subjects | 95 subjects |
| Vulnerable Subjects | (N/A) |
| Study Method | 1. Patients for whom the operation for the anal disease has been determined in the outpatient clinic are divided into a sitz bath group and bidet group through randomization prior to the surgery. This is a single-blind study and the investigator is unaware of which group the patients were assigned to. 2. From the next day after the operation for anal disease, perform a sitz bath or bidet at least once a day. It must be performed in the morning and can be additionally performed if there is a pain in the middle. 3. The pain is assessed before and after the use of a sitz bath or bidet for 4 weeks after surgery. The degree of pain is evaluated by a subjective Visual Analog Scale (VAS). Time to use a sitz bath or bidet is recorded. 4. Every week after surgery, the outpatient clinic visit is made to evaluate the healing of anal wounds. Complete wound healing requires that the wound area is epithelialized and there is no exudate. 5. As the primary endpoint, the difference in pain is compared and analyzed at 1 week. 6. As a secondary endpoint, a questionnaire survey for the difference in wound healing and the convenience of sitz baths and bidets after 4 weeks is conducted to analyze and compare. 7. As a secondary endpoint, evaluating the urinary function before and after surgery. |
| Efficacy Evaluation | 1. Primary endpoint - the degree of pain (VAS) after operation for anal disease 2. Secondary endpoints - wound healing and patient convenience, urinary function before and after surgery in men over 40 years old |
| Safety Evaluation | After the anal surgery, visit an outpatient clinic to perform anal visual inspection and palpation. Through this, adverse events or side effects that may occur due to bidet or sitz baths will be evaluated, and examinations are conducted considering the possibility of anal fissure, rectal prolapse, perianal burns. If an adverse event or side effect occurs, document and report it to the IRB, and report any serious adverse event (SAE) immediately. |
| Expected Effect and Predicted Outcome | The sitz bath is widely used in the treatment of anal diseases, but it is an undeniable fact that it is a very difficult treatment process for patients after surgery. The use of a bidet after anal surgery is not inferior to the use of a sitz bath in pain management and wound healing. It is thought that a bidet can be a substitute for a sitz bath if it is more convenient, and it can be used for pain and wound management after anal surgery as a more favorable method. |

([name])

Seoul National University College of Medicine Medical Education Research Foundation Designated Fund for Laboratory

1. **Estimated Study Duration**

2015.01.12 - 2019.01.11

1. **Indications to be studied**

the patients who undergo hemorrhoidectomy

1. **Study Background and Objectives**
2. **Study Background**

The sitz bath is usually recommended for hygiene and also as a therapeutic modality for the treatment of anorectal diseases. The patient seats on the basin or tub, and sinks their buttocks into the water, especially the perianal area, for a few minutes. In particular, a warm sitz bath could be helpful to reduce pains by reducing the anal pressure through relaxing the muscle and relieve congestion and edema by increasing the blood ﬂow to the perianal area. The effect of such a warm sitz bath has been proven through many studies for a long time, and it is essential for pain control and wound healing after operation for anal diseases [1-3].

A bidet is mainly used for cleansing the anal and perineal area [4-5]. Because it brings water in contact with the perianal area, similar to a sitz bath, many patients actually use a bidet at home, although there are few reports on its clinical use.

In previous studies, we have already reported that using a bidet in normal adults can effectively lower the anorectal pressure when using low water pressure and warm water [6]. It has been reported that if this effect of reducing the anorectal pressure is lower than that of the conventional commercial bidet, it can have the same effect as a sitz bath with a decrease in the initial anal pressure [7, unpublished].

Relieving pain after surgery is mainly performed by using analgesics, so sitz baths and bidets are limited to play a subsidiary role. However, it is thought that it can be helpful if it can be used conveniently. However, to use a bidet with the lowest force water stream as a substitute for a sitz bath for pain control and wound healing after anal surgery for patients in clinical practice, a randomized comparative clinical trial is necessary. In addition, since a sitz bath is helpful for patients who have urinary difficulty after surgery, we would like to compare it as a secondary endpoint whether the bidet is also effective for this.a4

1. **Study Hypothesis and Objective**

This study is intended to prove that, as a primary endpoint, the degree of pain in the case of using a bidet after operation for the anal disease is not inferior to compared to the conventional sitz bath. Also, as a secondary endpoint, we tried to demonstrate that there is no difference in wound healing within 4 weeks and the patient's convenience can be increased.

Therefore, in this study, we tried to compare and analyze the effect of pain control and wound healing after operation for anal diseases, the convenience, and urinary difficulty improvement with the conventional sitz bath by using a bidet with the lowest force water stream.

This trial is a study to compare and analyze whether a general home appliance bidet can replace the sitz bath therapy (using a sitz bath basin), which is generally used for pain control and wound management of patients after anal surgery. This is a comparative analytical study on the equivalent effect between sitz bath therapy using a sitz bath basin, not medical devices, and a bidet. It is not a clinical trial for the medical device.

1. **Code Name of Investigational Product or Investigational Device (or generic name of the active ingredient), Drug ingredients and quantities, Formulation, etc. (including control drug)**

N/A

(Bidet - Coway Clinic Bidet (BASH21-A) is used

It is a product that is currently marketed as a home appliance and is not a medical device. Instructions/manual is attached.)

1. **Inclusion Criteria and Exclusion Criteria, Target Number of Subjects and Rationales for Calculation**
2. **Inclusion Criteria**
3. 19 to 70 years old
4. Patients who need to undergo hemorrhoidectomy for hemorrhoids
5. Patients who are capable of understanding and conducting this clinical trial
6. **Exclusion Criteria**
7. Patients who have a previous history of anal surgery
8. Patients who underwent PPH for hemorrhoids
9. Crohn's anal disease
10. Complex anal fistula
11. Patients with uncontrollable medical diseases such as high blood pressure or diabetes
12. Active TB patients and patients taking TB drugs
13. HIV patients
14. Patients with a history of malignant tumors within the last 5 years
15. Patients receiving immunosuppressants
16. Pregnant or breastfeeding women
17. Patients with drug allergy
18. **Target Number of Subject and Rationale for Calculation**
19. Non-inferiority test

Reference 14 shows data that the warm water spray method could expect similar effects to the sitz baths. The bidet used in this study is assumed to be non-inferior to the sitz bath in improving post-operative pain. It is assumed that the average of the bidet group and the average of the sitz bath group were the same and the difference was 0.

On the other hand, in Reference 15, in post-OP pain of acute anal fissure, sitz baths showed a tendency to significantly reduce pain. Considering that pain decreases over time and almost disappears at 4 weeks, it can be said that it is a clinically valid approach to show that a bidet is not inferior to a sitz bath on the pain at 1 week. In the references, the average pain of the sitz bath group at 1 week was 22 and the standard deviation was 3.2 for the comparison data of overall pain in Figure 2. In the non-sitz bath group, the average pain was 29 and the standard deviation was 4.5. We try to obtain the number of subjects by substituting this value into the formula for calculating the sample size for the non-inferiority trial.

[figure not shown]

When α=0.025 and β=80%, Zα = 1.96 and Zβ = 0.85. When the non-inferiority margin, delta = 10%, the non-inferiority margin is 2.2, which is 0.1 times the average of 22 in the sitz bath group. That is, the upper limit of 95% of the distribution should not exceed 24.2 in the control group to prove non-inferiority. In the equation, σ is the standard deviation and λ is the non-centrality parameter. In this study, λ=1.

For the standard deviation, 3.2, which is the standard deviation value in the sitz bath group, is used.

The calculation result of the above equation is 34 subjects. Therefore, patient recruitment is continued until the size of FAS, the analysis set of the primary endpoint, reaches a total of 68 subjects (up to 34 per group).

1. **Recruitment Plan of Study Subjects**

For patients who visit the outpatient clinic for anal disease and are judged that anal surgery is necessary, the medical staff will explain this study and obtain consent to recruit study subjects. The principal investigator and sponsor of this study will not exclude patients who are possible to participate in this study based solely on race or socioeconomic status. All efforts will be made to ensure that patients who are eligible for the inclusion criteria can participate in this study, and will notify the objective of this study to patients so that they will represent the entire population of patients being treated at this institution.

Researchers [name] and [name], and professor [name] will be in charge of some parts of the study, such as recruitment of study subjects, consent process, data analysis, and preparation of the report. The overall monitoring will be performed by professor [name], who is not related to this study.

1. **Study Method**
2. **Detailed Study Method**
3. Patients for whom the operation for the anal disease has been determined in the outpatient clinic are divided into a sitz bath group and bidet group through randomization prior to the surgery. This is a single-blind study so that the investigator (operator) does not allow the patient to know which group the patient is allocated to.
4. From the next day after the operation for anal disease, perform a sitz bath or bidet at least once a day. It must be performed in the morning and can be additionally performed if there is a pain in the middle.
5. The pain is assessed before and after the use of a sitz bath or bidet for 4 weeks after surgery. The degree of pain is evaluated by a subjective Visual Analog Scale (VAS). Time to use a sitz bath or bidet is recorded.
6. Every week after surgery, the outpatient clinic visit is made to evaluate the healing of anal wounds. Complete wound healing requires that the wound area is epithelialized and there is no exudate.

In the outpatient clinic visit, the investigator should not ask the patient whether to use a sitz bath or bidet.

1. As the primary endpoint, the difference in pain is compared and analyzed at 1 week.
2. As a secondary endpoint, a questionnaire survey for the difference in wound healing and the convenience of sitz baths and bidets after 4 weeks is conducted to analyze and compare.
3. In addition, in men over 40 years of age, evaluating urinary function through a validated questionnaire before and after surgery (at the outpatient visit), respectively.

* CONSORT diagram

Randomization 🡪 bidet group, sitz bath group

(수술 전 외래 방문시)

Operation for anal disease

; Hemorrhoidectomy

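### The 80% power at 34 per group is reproducible, but it holds only if both arms have SD 3.2, a value carried to the bidet arm without justification and with no headroom

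*Protocol*

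**What the plan says.** All planning inputs stand in the Protocol under Target Number of Subject and Rationale for Calculation.

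- Error rates: "When α=0.025 and β=80%, Zα = 1.96 and Zβ = 0.85". The 80% labelled β is plainly the power.
- True difference: "the average of the bidet group and the average of the sitz bath group were the same and the difference was 0".
- Margin: "the non-inferiority margin is 2.2, which is 0.1 times the average of 22 in the sitz bath group".
- Control-arm source values: "the average pain of the sitz bath group at 1 week was 22 and the standard deviation was 3.2".
- Second group in the same source: "In the non-sitz bath group, the average pain was 29 and the standard deviation was 4.5".
- SD used: "For the standard deviation, 3.2, which is the standard deviation value in the sitz bath group, is used".

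The result is 34 per group, and recruitment runs until the full analysis set reaches 68. The source is introduced with the remark that "in post-OP pain of acute anal fissure, sitz baths showed a tendency to significantly reduce pain", and its values are described as overall pain.

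This trial enrols hemorrhoidectomy patients. Under Efficacy Evaluation Criteria, Evaluation Method, the primary endpoint is the VAS after the morning sitz bath or bidet use at one week. Data Analysis and Statistical Analysis Method plans t-tests on the weekly pain scores and names no covariate. Detailed Study Method says pain is assessed both before and after each use.

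**The concern.** With a margin of 2.2 and an assumed difference of zero, power depends on the SD alone once the group size is fixed. The section argues for equal means in the two arms. It gives no argument for equal spread, and no SD for the bidet arm is known. The value used also comes from a different operation and a different pain measure from the trial's own endpoint, and the Protocol does not say why it should transfer.

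The calculation leaves no room for error: 34 is the first whole number above the computed 33.4. Any SD above 3.2 in either arm therefore takes power below or further below 80%. The price would be a higher chance that a bidet truly equal to the sitz bath fails to be shown non-inferior. A reader of the section cannot see that the 80% depends on this one choice.

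**Working it through.** **Inputs.** Margin 2.2; true difference 0; one-sided α 0.025 (z = 1.96); power 80% (z = 0.85 in the Protocol); n = 34 per group; SDs 3.2 and 4.5. All are from the sample-size section. The printed formula is a figure that is not shown, so the standard two-sample formula is used. The section also says "In this study, λ=1"; it calls λ a non-centrality parameter, and here it is read as 1:1 allocation.

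**Formulas.**

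- n per group = (1.96 + 0.85)² × (s₁² + s₂²) / 2.2²
- SE = √((s₁² + s₂²)/34)
- power (normal) = Φ(2.2/SE − 1.96). The t value uses the noncentral t with 66 df.

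**Reproducing the plan.** n = 7.896 × 20.48 / 4.84 = 33.4, so 34. SE = √(20.48/34) = 0.776; 2.2/0.776 = 2.835; Φ(0.875) = 80.9%. By noncentral t it is 79.8%. The stated figure reproduces.

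**Is 4.5 tied to the higher mean?** SD over mean is 3.2/22 = 14.5% with sitz baths and 4.5/29 = 15.5% without. Applying 15.5% to a mean of 22 gives 4.5 × 22/29 ≈ 3.4.

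**Range at 34 per group.**

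| SD sitz bath / SD bidet | SE | Power, normal | Power, t | n per group for 80% |
|---|---|---|---|---|
| 3.2 / 3.2 | 0.776 | 80.9% | 79.8% | 33.4, so 34 |
| 3.2 / 3.4 | 0.801 | 78.5% | 77.3% | 35.6, so 36 |
| 3.4 / 3.4 | 0.825 | 76.1% | 74.8% | 37.7, so 38 |
| 3.2 / 4.5 | 0.947 | 64.2% | 62.9% | 49.7, so 50 |

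The last row is equivalent to a common SD of √((3.2² + 4.5²)/2) = 3.90.

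**What adjustment could return.** In an ANCOVA the residual SD is SD × √(1 − ρ²), where ρ is the correlation between the VAS before first use and the week-1 VAS. The Protocol gives no value, so ρ = 0.3 to 0.5 is assumed. The factor is √(1 − 0.09) = 0.954 or √(1 − 0.25) = 0.866. Normal approximation, 34 per group:

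| Unadjusted SD | No covariate | ρ = 0.3 | ρ = 0.5 |
|---|---|---|---|
| 3.2 | 80.9% | 84.4% (residual SD 3.05) | 90.5% (2.77) |
| 3.90 | 64.2% | 68.3% (3.72) | 76.5% (3.38) |

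All these powers are for the two-sample comparison that underlies the sample-size formula. The analysis section words its criterion as an upper limit for the bidet group set against a value 10% above the sitz bath mean. That wording is a separate matter and is not what these figures describe.

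**The case against.** The best defence is that the Protocol chose its SD openly and for a stated reason. The 3.2 belongs to the sitz bath group, which is this trial's control arm. The 4.5 belongs to patients without sitz baths, at mean 29, and no such arm exists here. If the bidet behaves like the sitz bath, using one SD for both arms is coherent. Because the two SDs are nearly the same fraction of their means, most of the gap between them may simply follow the higher mean. On that reading the shortfall is about 2 to 5 points (80.9% against 78.5% or 76.1%), not 17.

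Most of this stands, and it limits the point. A reader might infer that the sample size is miscalculated; it is not. A reader might infer that the trial's real power is 63%, or that 3.9 should become the planning SD. The documents support neither, since that scenario pairs the sitz bath mean with the spread of a group outside the trial. SD 4.5 in both arms has less support still, because it discards the control-arm value. Doubts about whether the source reported SDs, or about how many patients it had, cannot be raised from the Protocol: it calls the values standard deviations and gives no sample size.

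The defence does not supply a reason for equal spread in the bidet arm or for transfer from anal fissure to hemorrhoidectomy, and it does not create headroom. Nor do the 95 subjects in the Summary, because the sample-size section ties recruitment to 68 in the full analysis set.

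**Conclusion.** The point holds as a matter of an undisclosed condition and missing sensitivity, not as an error. The 80% at 34 per group is correct if both arms have SD 3.2. It falls to about 75 to 78% if the SD is about 3.4 in one or both arms, and to about 63 to 64% if the bidet arm has SD 4.5. The last is an adverse scenario that marks the lower end of a reasonable range.

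These figures assume a true difference of zero, a margin of 2.2, 34 analysed per group and a two-sample comparison at one-sided 0.025. Which SD will apply cannot be settled from the Protocol. The gain from covariate adjustment rests further on the assumed correlation of 0.3 to 0.5.

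**What to change.** 1. **Sample-size section.** State that 80% power is conditional on SD 3.2 in both arms, and show the range: about 75 to 78% with SD about 3.4 in one or both arms, and about 63 to 64% with 3.2 and 4.5. Say why 3.2 is expected to apply to the bidet arm and to the morning VAS after hemorrhoidectomy, or say that this is an assumption. There is no need to adopt 3.9 as the base value.

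2. **Data Analysis and Statistical Analysis Method.** Replace the unadjusted week-1 t-test with a between-group difference and 95% CI from an ANCOVA, adjusting for the VAS recorded before the first sitz bath or bidet use, and judge its upper limit against 2.2. That reading follows randomization but precedes any use of the assigned method. Its correlation with week-1 pain is uncertain, partly because it falls close to the analgesia given around surgery, so no specific gain should be promised.

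The cost is a less favourable statement of power and slightly more analysis work. No extra patients are needed, and no new measurement, since pain before use is already collected.

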**Bidet group**

Use of bidet from the day after surgery

; warm water, low water pressure (less than 4 gf)

(Install the same bidet in the hospital and at home)

**Sitz bath group**

Warm sitz bath from the day after surgery

**Comparative Evaluation of Efficacy**

**1) Pain (scoring)**

**2) Wound healing period (outpatient follow-up)**

**3) Patient convenience (questionaire)**

* Sitz Bathing Method

1. Urinate in advance.

2. Fill with the warm water of 38-40°C in half of the sitz bath basin.

(The water temperature should be warm when soaking the elbow, and if there is too much water, the water will overflow when to sit your buttocks in a sitz bath basin.)

3. Check the front and back of the sitz bath basin and place it on the toilet.

4. Soak anus in a sitz bath basin and sit for 3-5 minutes.

5. After sitz bathing, gently wipe dry around the anus with a towel. In some cases, you can also use a dryer. (It is important to dry thoroughly)

[figure not shown]

* Bidet Method

1) Sit on the bidet with the lowest water pressure.

2) Press the sitz bath button to bring water flow into contact with the anal wound area for about 3 to 5 minutes.

3) Dry off the anal area.

[figure not shown]

1. **Control Group Setting and Randomization Method**

Randomization is performed using the sitz bath group as a control group. By requesting the Seoul National University Medical Research Collaborating Center (MRCC), a randomization table is created in advance. On the MRCC home page, a web-based randomization system is used to check the patient allocation group the day before surgery and conduct patient education.

1. **Study Drug Administration Dosage, Method of Administration, Combination Therapy, Reasons for Selection when using Control Drug**

Ketorolac tromethamine

It is a general analgesic used for pain in the wound area after surgery, iv 30mg prn (90mg/day) is used on the day of surgery and until the morning of the next day, and 1T (10mg) tid (prn qid) is used for 5 days from the afternoon of the next day of surgery. (However, when the hospitalization period is different depending on the hospital, a PCA device using ketorolac (90mg/day) can be used during the hospitalization period of 3 to 4 days. An oral analgesic is prescribed at the time of discharge)

At the outpatient visit 7 days after surgery, the remaining analgesics will be collected and recorded the amount.

1. **Observation Items, Clinical Laboratory Items, and Observation Test Methods**
2. Primary endpoint – the degree of pain after operation for anal disease
3. Secondary endpoint - wound healing and convenience of performance
4. Secondary endpoint- questionnaires on the degree of urinary difficulty improvement (IPSS), men over 40 years old (subgroup analysis)
5. **Efficacy Evaluation Criteria, Evaluation Method**
6. Primary endpoint evaluation method – The degree of subjective pain is evaluated by the Visual Analog Scale (VAS). The patient records the degree of pain after taking a sitz bath or bidet at a certain time every day (right after waking, 7-8 am). After a week, the degree of pain (after using a sitz bath or bidet immediately after waking up) is used as the primary endpoint for comparative analysis.
7. Secondary endpoint evaluation method- Also, the degree of pain reduction is performed the linear comparative analysis as a continuous variable.
8. Secondary endpoint evaluation method - Every week after anal surgery, the outpatient clinic visit is made to get an anal examination. The physician in the outpatient clinic should confirm complete epithelialization and no exudate from the anal wound through visual inspection and palpation, and it is determined as a complete healing.
9. Secondary endpoint evaluation method – Convenience in performing sitz baths and bidets is investigated through a questionnaire (attached) at 4 weeks after surgery.
10. Secondary endpoint evaluation method – For men over 40 years old, a questionnaire on urinary difficulty is completed and evaluated when visiting the outpatient clinic every week.
11. **Differences from Existing Treatments and Researches**

Conventional sitz baths performed after anal surgery is a very cumbersome and difficult process to ﬁll a small tub with water, place it on a toilet, and drain the water after taking sitz baths, so it is a very difficult procedure for patients to perform for 3 to 4 times a day. Therefore, the elderly or disabled with limited mobility cannot do it without the help of a guardian. Like a sitz bath, bidet brings water into contact with the perianal area. Because of similarities between the sitz bath and the bidet, questions are raised whether a bidet can be used instead of a sitz bath. The investigator suggested that bidets can have the same effect as sitz baths in previous studies. If the use of such a bidet has a similar effect to the sitz bath after anal surgery, the patient who has undergone anal surgery can conveniently use a bidet instead of a sitz bath. These effects of the bidet have not been studied up to date, so it is expected that this study can compare and analyze the pain relief effect between bidets and sitz baths after anal surgery.

1. **Benefits and Risks to Study Subjects

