Recruitment of study subjects, consent process, data analysis, and report preparation for this study will be conducted under the supervision of the person in charge of monitoring who has no conflict of interest with this study.

1. **Data Analysis and Statistical Analysis Method**

Data and statistical analysis will be conducted with the help of MRCC.

Establishment of analysis set: Data analysis is performed by dividing the full analysis set (FAS) and the PP set.

According to ICH E9, FAS is an analysis set that is as close as possible to the concept of the intention-to-treat (ITT) principle and it can exclude the least number of subjects from the analysis for justifiable reasons from all randomized subjects. The reasons for excluding a subject from the analysis target group without the possibility of introducing bias are under the following circumstances.

① Subjects who violate the criteria for inclusion/exclusion of subjects

② Subjects who have never received the study drug

③ Subjects with no data after randomization

In the case of ② and ③, the excluded subjects were due to dropout caused by schedule adjustments with the visiting technician during the installation of a bidet after surgery, and it is expected that there is no relation to the treatment effect. However, to determine whether there are potential biases that may occur by excluding them, we will check whether the underlying characteristics collected during the screening process differ from those included in the analysis.

The PP set consists of subjects who performed sitz baths or bidets as assigned to at least 80% of the set schedule.

The primary endpoint is determined by the FAS.

Analysis of the underlying characteristics and questionnaire of the two groups: Continuous variables are presented using t-test and categorical variables are compared using the chi-squared test. Pain scores are compared for each week using a t-test. Bonferroni correction is implemented in consideration of the expansion of Type I error due to multiple comparisons. For the pain score in the first week after surgery, it is confirmed that the upper limit of 95% of the bidet group is less than the value 10% higher than the average value of the sitz bath group.

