Analysis of adverse events and side effects: Identify the frequency of each side effect and check whether there is a significant difference between the two groups through the Fisher test. Analysis of side effects will be performed on all subjects who have conducted a bidet or sitz bath even once.

A statistical test is conducted in a two-tailed test and a p-value less than 0.05 is considered significant.

1. **Study Schedule**

|  | December | January | February | March | April | May | June | July | August | September | October | November |
| --- | --- | --- | --- | --- | --- | --- | --- | --- | --- | --- | --- | --- |
| Building a network of participating hospitals |  |  |  |  |  |  |  |  |  |  |  |  |
| Recruitment of subjects |  |  |  |  |  |  |  |  |  |  |  |  |
| Clinical trial |  |  |  |  |  |  |  |  |  |  |  |  |
| Results analysis and interim reporting |  |  |  |  |  |  |  |  |  |  |  |  |
| Preparation of paper |  |  |  |  |  |  |  |  |  |  |  |  |
| Paper presentation and result report |  |  |  |  |  |  |  |  |  |  |  |  |

1. **Measures for the Safety Protection of the Subjects**
2. **Basic Principal for Ensuring Research Ethics**

This study will comply with the Helsinki Declaration and ICH-GCP revised in 2013 and will be conducted following the protocol approved by the Institutional Review Board (IRB). The purpose and content of the study are explained to the subjects, and only applicants who know and consent to the purpose of this study will participate in the study. Participants in the study can discontinue the trial at any time during the trial and also have been aware of this. There are no special disadvantages to participants related to this study, and the confidentiality of medical information will be maintained. Documents containing the patient's personal information will be retained by encrypting and enclosing in the office of the professor in charge. Access is prohibited except for the investigators involved in this study.

1. **Subjects’ Consent Process**

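### The urinary endpoint (IPSS in men over 40) is scored before surgery and weekly, but the only stated analysis is an unadjusted t-test, with no deciding visit and no stated use of the pre-operative score

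*Protocol*

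**What the plan says.** The urinary endpoint is described in four places in the protocol:

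- **Summary, Study Method:** "As a secondary endpoint, evaluating the urinary function before and after surgery". The Efficacy Evaluation row limits this to men over 40.
- **Detailed Study Method:** "evaluating urinary function through a validated questionnaire before and after surgery (at the outpatient visit), respectively".
- **Observation Items:** "questionnaires on the degree of urinary difficulty improvement (IPSS), men over 40 years old (subgroup analysis".
- **Efficacy Evaluation Criteria, Evaluation Method:** "For men over 40 years old, a questionnaire on urinary difficulty is completed and evaluated when visiting the outpatient clinic every week".

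Visits are weekly: "Every week after surgery, the outpatient clinic visit is made to evaluate the healing of anal wounds". Follow-up lasts four weeks: "The pain is assessed before and after the use of a sitz bath or bidet for 4 weeks after surgery". That gives one pre-operative score and about four post-operative ones.

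Data Analysis and Statistical Analysis Method gives the test: "Analysis of the underlying characteristics and questionnaire of the two groups: Continuous variables are presented using t-test", with chi-squared for categorical variables. The same paragraph then has pain compared week by week with a t-test, states a Bonferroni correction for multiple comparisons without naming the family or divisor, and returns to the week-1 pain rule. The section closes with a general two-sided rule: "a p-value less than 0.05 is considered significant".

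**The concern.** The endpoint has a built-in baseline, but the stated test does not mention it. A t-test could be run on the post-operative score or on the change from before surgery, and at any of four visits; the protocol does not choose. It does choose for other endpoints: pain is judged at one week and convenience at four.

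Two things are at stake. The first is precision. The endpoint is confined to men over 40 in a trial whose full analysis set is planned at 68, so the subgroup is small, and a test that ignores the pre-operative score, or uses it inefficiently, wastes information already collected. The second is interpretability. With several visits and two possible quantities, a reported p-value is hard to read unless the deciding comparison was fixed beforehand.

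**Working it through.** **The plan's own figure.** The protocol gives no sample size, power or error rate for the urinary endpoint. Its only such figure is for the primary pain endpoint (margin 2.2, SD 3.2, z-values 1.96 and 0.85, equal allocation):

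2 × (3.2 × (1.96 + 0.85) / 2.2)² = 33.4, rounded up to 34 per group, 68 in total.

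This reproduces the stated number and does not depend on the urinary analysis.

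**Inputs.** From the protocol: weekly visits over four weeks, hence four post-operative scores (derived); two-sided 0.05; t-test for continuous questionnaire data. Assumed, because the protocol does not give them: the correlation r between pre- and post-operative IPSS, the correlation between weekly test statistics, equal variances before and after surgery, and IPSS treated as continuous.

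**Step 1: gain from using the pre-operative score.** Relative variance of the between-arm difference, with the post-operative score alone set to 1:

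- change score: 2(1 − r)
- ANCOVA: 1 − r²

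| r | post only | change | ANCOVA |
|---|---|---|---|
| 0.3 | 1 | 1.40 | 0.91 |
| 0.5 | 1 | 1.00 | 0.75 |
| 0.6 | 1 | 0.80 | 0.64 |
| 0.7 | 1 | 0.60 | 0.51 |
| 0.8 | 1 | 0.40 | 0.36 |

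Since 2(1 − r) − (1 − r²) = (1 − r)², ANCOVA is never worse than the change score on these formulas. They ignore the one degree of freedom spent on the covariate.

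Reduction in standard error at r = 0.6 and 0.7:

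- Against the post-operative score: 1 − √0.64 = 20% and 1 − √0.51 = 29%. The equivalent sample-size factors are 1/0.64 = 1.56 and 1/0.51 = 1.96.
- Against the change score: 1 − √(0.64/0.80) = 11% and 1 − √(0.51/0.60) = 8%. The factors are 0.80/0.64 = 1.25 and 0.60/0.51 = 1.18.

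**Step 2: error rate if all four weeks are tested.** With independent tests:

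- each at 0.05: 1 − 0.95⁴ = 18.5%
- each at 0.05/4 = 0.0125: 1 − 0.9875⁴ = 4.9%

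Scores from the same men are correlated, so the relevant values are lower. Simulating four equally correlated two-sided z-tests with no true difference (400,000 draws) gives the chance of at least one significant result:

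| correlation | each at 0.05 | each at 0.0125 |
|---|---|---|
| 0.5 | 15.6% | 4.3% |
| 0.7 | 13.0% | 3.7% |
| 0.8 | 11.4% | 3.2% |

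The left column applies only if all four weeks are tested and Bonferroni is confined to pain. The right column applies if Bonferroni covers the urinary scores with a divisor of four.

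**The case against.** A reader might infer three stronger things; the document supports none of them.

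- **That the sections contradict each other on timing.** No section says there is only one post-operative assessment. Before and after surgery, at the outpatient visit, fits a pre-operative score followed by weekly scores; the evaluation section then simply adds detail.
- **That the pre-operative score is thrown away.** The Observation Items section calls the endpoint improvement on IPSS, and a t-test on change would satisfy both that wording and the analysis section. Only a statement of how the score is used is lacking.
- **That the error rate is inflated.** Four uncorrected weekly urinary tests are not written down. The section has the questionnaire completed and evaluated weekly, which may mean no more than assessment. The Bonferroni sentence sits between two pain sentences, so the natural reading is pain only, but its paragraph opens with questionnaires and it names no family. If weekly testing extends to IPSS, the correction may well extend with it.

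It can also be said that an unadjusted t-test is valid in a randomised comparison, and that the choice of visit and of covariates is often left to a statistical analysis plan, which was not at hand. The first is true, so the case for ANCOVA is one of precision, not validity. The second would dispose of a complaint that a visit is merely unnamed. It does not dispose of the whole point, because the protocol itself fixes a test for questionnaire data, and a better one is available from data already planned.

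**Conclusion.** The point holds as an improvement to a stated method. For a baseline-measured score in a small subgroup, an unadjusted t-test is weaker than ANCOVA on the pre-operative IPSS, whether the t-test is run on the post-operative score (standard error 20-29% lower with ANCOVA) or on change (about 8-11% lower). These figures rest on assumed pre/post correlations of 0.6-0.7. The size of the subgroup is not stated, so its power cannot be computed.

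Error inflation is conditional: about 11-16% under the narrow reading of Bonferroni with four tests and assumed between-visit correlations of 0.5-0.8, and at or below 5% under the broad reading. The endpoint is secondary and labelled a subgroup analysis. The primary non-inferiority conclusion and the 34 per group are untouched.

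**What to change.** In Efficacy Evaluation Criteria, Evaluation Method and in Data Analysis and Statistical Analysis Method, state one urinary analysis for men over 40. Either:

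1. compare the arms on IPSS at one named post-operative visit by ANCOVA adjusted for the pre-operative IPSS, and report the other weeks descriptively (the one-week visit would match the primary pain time point); or
2. fit one repeated-measures model to all the weekly scores, adjusted for the pre-operative IPSS, with a single test of arm.

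Also say which tests the Bonferroni correction covers and with what divisor.

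The cost is wording only, since all the scores are already to be collected. The small downside is that the other visits no longer carry a significance claim of their own.
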